Each of the interventions listed in Table 1 addresses a unique population of patients within a clinic, with the exception of interventions 4-6, which are substitutes for one another. For example, fast track initiation counseling is limited to patients eligible to start treatment; enhanced adherence counseling is limited to patients failing treatment; early tracing of missed appointments is limited to patients who are late for scheduled visits; and so on. While individual patients may become eligible for multiple interventions over the course of their care, the interventions will not serve overlapping cohorts of patients simultaneously. This will allow the impact of each intervention to be evaluated separately, as well as within the overall package.

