## **e. Early Tracing of Patients Lost to Follow Up**

Early tracing of patients who miss an appointment by 5 days or more seeks to identify patients who have not returned to the clinic for scheduled appointments and attempts to return them to care. This intervention requires obtaining permission from patients to contact them and maintaining up to date contact information in patient records. The goal is to reduce clinic loss to follow up and improve patient outcomes by identifying those who have missed appointments and seeking to encourage them to return to care.

| *Primary outcome:* | Proportion of patients who miss a scheduled appointment by 5 days or more who return to care within 3 months of tracing |
| --- | --- |
| *Eligibility:* | All adult patients who fail to return for a scheduled appointment within 5 to 90 days from their appointment date |
| *Sample size:* | 576 (288 per arm; 24 per cluster) |
| *Data sources:* | Tier.Net; tracing registers or logbooks; appointment books; consent forms; other registers or records that document tracing attempts and interactions with patients |

In the early implementation phase at the study clinics, the government will also test fast track/spaced appointments for patients on antiretroviral therapy. This strategy is targeted at patients who are stable on treatment as defined above and therefore does overlap with the adherence club and decentralized medication delivery populations. If fast track/spaced appointments are implemented for the same patients enrolled in the adherence clubs or receiving decentralized medication delivery in the pilot facilities, the interventions evaluated will then be “adherence clubs plus fast tracked/spaced appointments” and “decentralized medication delivery plus fast tracked/spaced appointments,” as it will not be possible to distinguish between the impacts of the two interventions.

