## **b. Inclusion and Exclusion Criteria**

For Objectives 1-5 and Objective 8, we will enroll a specific cohort of patients. These will be numbered in accordance with the objective number for Objectives 1-5; for Objective 8, the cohort will be called the “TBHD cohort”, in reference to tuberculosis, hypertension, and diabetes. This TBHD cohort will be made up of patients who have been screened for TBHD (50%) and patients who are newly diagnosed with TB, hypertension or diabetes (50%). For all cohorts, inclusion and exclusion criteria are as shown below. For Objectives 1-5, these criteria follow the December 2014 national guidelines for HIV care and ART[10] and November 2015 National Adherence Guidelines for Chronic Disease (HIV, TB and NCDs) [11].

*Cohorts 1-5 and TBHD cohort inclusion criteria*

- ≥ 18 years old
- Meet the inclusion criteria for one or more of Cohorts 1-8

*Cohorts 1-5 and TBHD cohort exclusion criteria*

- Not resident in the facility’s catchment area
- Recorded intention to transfer care to a different facility within 12 months
- Pregnant and eligible for PMTCT

*Objective 1/Cohort 1 inclusion criteria (Patients newly eligible for ART—fast track treatment initiation)*

- Determined to be eligible to start ART under prevailing national guidelines (CD4 count < 500, WHO Stage 3 or 4 condition, TB, cryptococcal meningitis)

*Objectives 2 and 3/Cohorts 2 and 3 inclusion criteria (Patients stable on ART—adherence clubs or decentralized medication delivery)*

- On same ART treatment regimen for at least 12 months
- Most recent viral load taken in past 6 months
- Two consecutive viral loads undetectable (<400 copies/ml^3^)

*Objective 4/Cohort 4 inclusion criteria (Patients on ART with poor adherence—enhanced adherence counseling)*

- On first line ART for at least 6 months
- Poor adherence as indicated by an elevated viral load (>400 copies/ml^3^)

*Objective 5/Cohort 5 inclusion criteria (Patients lost from ART programs—early patient tracing)*

- Initiated ART
- Fail to return for a scheduled appointment within 5 to 90 days from their appointment date

*Objective 8/TBHD cohort inclusion criteria (Tuberculosis, hypertension, and diabetes patients)*

- Screened for or diagnosed with for TB or hypertension within the last month, or diabetes within last 6 months

*Objective 8/TBHD cohort exclusion criteria (Tuberculosis, hypertension, and diabetes patients)*

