## **c. Data Analysis Objectives 1-5**

Our general analytic plan will be the same for each of Cohorts 1-5. We will begin with descriptive analyses of the characteristics of each of the cohorts stratified by intervention/non-intervention (comparison) cohorts. We will also look for differences within the randomized matched pairs. Because the data will be collected as part of a clustered design, the data analysis will need to account for clustering. For each primary outcome described above, we will conduct a crude analysis comparing the proportion of subjects with the outcome in the intervention and comparison arms. Next we will conduct an analysis for each outcome accounting only for clustering using generalized estimating equations (GEE) with an unstructured correlation matrix and clustering by treatment site. In all cases the outcomes are dichotomous and therefore we will calculate relative risks comparing the intervention to the comparison arms using a log link function and a binomial distribution. Next, should any imbalances between treatment groups be detected, we will adjust for those covariates in our GEE model. Finally, we will look for differences in the effects of the strategies by important baseline characteristics (e.g. size of the treatment population, rural vs. urban, province, etc.) using stratified analyses.

We note that because each of the interventions is targeted at a different population with the exception of decentralized medication delivery and adherence clubs, which would not be delivered to the same people at the same time, we can estimate the impact of each intervention separately, as only one of them will be delivered to each cohort within a clinic at any one time. Since some patients may participate in more than one intervention (e.g. fast track initiation followed by tracing), we will conduct a sub-analysis restricted to those who received only one intervention to look for the effects of each intervention by itself.

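### The claim that each intervention's effect can be estimated separately does not fit a design that randomises the package as a whole, and the planned one-intervention sub-analysis does not repair it

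*Protocol*

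**What the plan says.** Section 10c (Data Analysis Objectives 1-5) concludes that the impact of each intervention can be estimated separately, "as only one of them will be delivered to each cohort within a clinic at any one time". Section 3b (Rationale) gives the same premise: "the interventions will not serve overlapping cohorts of patients simultaneously". Among the interventions of Table 1 it makes one exception, "with the exception of interventions 4-6, which are substitutes for one another". Counted through the table, these are adherence clubs, spaced and fast-lane appointments, and decentralised delivery.

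The protocol also qualifies the premise:

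- Section 3b grants that "individual patients may become eligible for multiple interventions over the course of their care".
- The sentence after the separability claim in section 10c reads: "Since some patients may participate in more than one intervention (e.g. fast track initiation followed by tracing), we will conduct a sub-analysis". Its purpose is given as "a sub-analysis restricted to those who received only one intervention to look for the effects of each intervention by itself".
- Section 4e says that the spaced-appointment strategy "therefore does overlap with the adherence club and decentralized medication delivery populations". If it is given to the same patients, the evaluated intervention is renamed as the combination, because the two impacts could not be told apart.
- The introduction to section 4 promises an effect for each intervention individually, but within implementation of the whole package.

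Under section 8b, tracing is for patients who have started ART and who "Fail to return for a scheduled appointment within 5 to 90 days from their appointment date". Enhanced counselling is for patients with at least six months on first-line ART and a viral load above 400. Neither rule excludes members of other cohorts. Under section 8a, one clinic of each pair receives the package and the other continues standard of care.

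**The concern.** The separability sentence carries the interpretation of Objectives 1 to 5, because the research questions in section 3c ask for the effect of each named intervention. Section 10a makes the long-term outcomes part of the primary outcomes. Retention and viral suppression at 9 or 12 months are exactly what tracing and repeat counselling aim to change. If those components come with the package, a difference between arms in the Fast Track or club cohort may be partly their work.

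The consequence reaches two later objectives. Section 10d weights intervention effects by the population eligible for each, so a benefit of tracing could count in Cohort 5 and again in Cohorts 1-4. Section 10e derives a cost per patient achieving the primary outcome for each intervention, which depends on attributing those outcomes to it.

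**Working it through.** The point contests a statement, not a figure, so there is no number in the plan to reproduce. The sections are compared first. The arithmetic after that is for scale only.

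**1. What the arm contrast contains.** The randomised unit is the clinic and the randomised treatment is the package. Within a cohort, intervention minus comparison is therefore the named intervention plus any other package component its members receive before the outcome date, against standard of care.

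**2. Which outcomes are exposed** (eligibility from sections 4 and 8b, outcomes from Table 3):

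| Cohort | Outcome | Other components that can act first |
| --- | --- | --- |
| 1 Fast track | ART start by 30 days | Largely none: under section 8b tracing requires ART to have begun |
| 1 Fast track | 9-month outcome | Tracing after ART start; enhanced counselling after six months on first-line ART, if viral load is elevated |
| 2 and 3 Clubs, delivery | Medication at 4 and 3 months | Tracing from day 5 of lateness; spaced appointments |
| 2 and 3 Clubs, delivery | 12-month suppression | The same, plus enhanced counselling if on first-line ART with elevated viral load |
| 4 Enhanced counselling | 3 and 12 months | Tracing |
| 5 Tracing | 3 and 12 months | Tracing is the evaluated intervention, so no tracing carry-over |

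**3. Section 3b against section 4e.** Section 3b treats clubs, spaced appointments and delivery as alternatives to one another. Section 4e allows spaced appointments to be added to either of the others in the same patients. Both cannot describe the same implementation.

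**4. Scale of carry-over.** The documents give neither the share of each cohort traced nor the effect of tracing on that cohort's outcome. Assume that 10% to 40% are traced, that tracing adds 5 to 15 points among those traced, and that comparison clinics do no equivalent tracing. The 15 is the Objective 5 design difference in Table 4.

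Carry-over = share traced × effect among those traced

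- Low: 0.10 × 5 = 0.5 points
- High: 0.40 × 15 = 6.0 points

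Against a 15-point design difference this is 0.5/15 = 3% to 6/15 = 40%.

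**5. Could that alone give a significant result?** Take Objective 1's design values: 12 clusters per arm, 30 per cluster, coefficient of variation 0.1 and a 60% control rate. The 60% is the 30-day initiation rate, borrowed because no 9-month rate is given. Alpha 0.05 is taken as two-sided and the matching is ignored. For a carry-over d:

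s² = [0.60×0.40/30 + (0.60+d)(0.40−d)/30 + 0.1²(0.60² + (0.60+d)²)]/12

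P(significant) = 1 − Φ(1.96 − d/s) + Φ(−1.96 − d/s)

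For d = 0.06, s² = (0.00800 + 0.00748 + 0.00796)/12 = 0.00195, so s = 0.0442, d/s = 1.36 and P is about 27%. For d = 0.015, 0.03 and 0.045, P is about 6%, 10% and 18%.

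**6. The restricted sub-analysis.** Suppose no intervention works. Assume 90% success among patients who never miss a visit and a rate r of 30% to 60% among those who do. Let a share f miss a visit and be traced. Dropping traced patients from the intervention arm leaves 90% there. The comparison arm, kept whole, has f×r + (1−f)×0.90. The spurious gain is f(0.90 − r):

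- f = 0.10: 3 to 6 points
- f = 0.20: 6 to 12 points
- f = 0.40: 12 to 24 points

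Under these assumptions the selection bias can exceed the carry-over it is meant to remove.

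**The case against.** The strongest reply is that the protocol already concedes most of this. Sections 3b and 10c acknowledge later receipt of more than one intervention, and tracing after Fast Track is the protocol's own example. What is denied is simultaneous delivery, and tracing after a missed visit comes later. Section 4 frames each effect within the package, and Objective 6 addresses the combined effect. The spaced-appointment overlap is disclosed, conditional and handled by renaming. Spaced appointments are also not among the five evaluated interventions, so they do not strictly contradict the section 10c sentence.

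Much of that stands, and it limits the point. A reader might infer that tracing is given alongside the named intervention to whole cohorts, in intervention clinics only, and that long-term effects will be credited to the wrong intervention. The documents do not support that reading. Tracing reaches only patients who miss a visit. The protocol does not say that comparison clinics do no tracing, and section 8a notes that most clinics already give some adherence support. Nor can Table 4's 15 points be carried over one for one as an estimate. It is a difference in return within three months, whereas Objective 1's long-term outcome also requires viral suppression, and loss to follow-up under section 10a means 90 days without attendance.

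The downstream effect is also narrower than it may look. Objective 6's primary outcome uses the short-term outcomes, and Objective 7's primary outcome is cost per patient receiving an intervention, which needs no attribution of effect.

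The reply does not rescue the separability claim. Outcomes are measured up to 12 months after entry, so later receipt inside that window contributes to the contrast just as simultaneous receipt would. Section 4 still promises each effect individually. Renaming covers spaced appointments but not tracing or enhanced counselling. The sub-analysis relies on a characteristic that arises after randomisation, and the protocol defines no matching restriction for comparison patients.

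**Conclusion.** The separability statements in sections 3b and 10c are not supported by the design. For Cohorts 1-4 the 9- and 12-month contrasts estimate the named intervention together with other package components received, and cannot be attributed to the named intervention alone. The 3- and 4-month outcomes of Cohorts 2-4 can be affected too. Cohort 1's 30-day initiation outcome is largely protected, and Cohort 5 has no tracing carry-over.

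The size cannot be derived from the documents. The range of 0.5 to 6 points rests wholly on the assumed shares and effects, and it would shrink to the extent that comparison clinics also trace. The contribution of spaced appointments cannot be bounded at all. The randomised comparison of the package in each cohort is not invalidated by this; what fails is its interpretation as the effect of one intervention. The restricted sub-analysis cannot supply that interpretation and may add bias of its own.

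**What to change.** - Delete or qualify the separability statements in sections 3b and 10c.
- State the Cohort 1-4 estimates, other than Cohort 1's 30-day initiation, as the effect of the minimum package in patients who enter as newly eligible for ART, stable on ART, or with an elevated viral load.
- For each cohort and arm, report the share who received each other intervention before each outcome date. Section 9b already lists dates of intervention eligibility and receipt.
- Label the one-intervention sub-analysis as non-randomised and exploratory.
- Reconcile section 3b with section 4e on whether spaced appointments replace clubs and decentralised delivery or may be added to them.
- Carry the same caveat into the intervention-specific effects used for Objective 6 and the cost-per-outcome figures of Objective 7.

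The cost is wording and one descriptive table from data already planned. The downside is a more modest attribution claim for the individual interventions.

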## **d. Data Analysis Objective 6**

To provide an indicator of the overall (combined) effect of the package of interventions, we will analyze patient retention in care within intervention and comparison groups overall. We will include interaction terms between site and intervention to determine whether different packages of interventions produce different cumulative effects. Then, using available data on the population of patients eligible for each intervention at each site, we will weight the effects of the interventions in proportion to population to produce an estimate of the proportion of population in need expected to benefit from the interventions at each site.

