- What is the effect of Enhanced Adherence Counselling on rates of being alive, in care, and virally suppressed within 3 and 12 months of intervention eligibility?

*Objective 5: Among HIV-infected patients in antiretroviral therapy programs who miss a scheduled appointment by 5 days,* ***evaluate the impact of Early Patient Tracing on retention in care****.*

Research questions:

- What is the effect of Early Patient Tracing on rates of returning to care by 3 and 12 months of tracing?
- What is the effect of Early Patient Tracing on rates of remaining in care by 12 months of tracing?

*Objective 6: For each clinic included in the study,* ***evaluate the overall impact of the Adherence Guidelines on patient outcomes****.*

Research questions:

- What is the effect of the package of interventions on patient retention in care overall?
- What is the proportion of population in need expected to benefit from the package of interventions?

*Objective 7:* ***Estimate the incremental and total cost of each of the interventions*** *listed above compared to standard of care.*

Research questions:

- What is the average cost per patient reached with the intervention?
- What is the average cost per successful outcome achieved?

*Objective 8:* ***Describe the current status of the cascade of care and adherence to treatment for tuberculosis, hypertension, and diabete****s, for the purpose of tailoring the minimum package of interventions to these conditions in the national rollout.*

Research questions:

- What is the prevalence of previously and newly diagnosed TB, hypertension, and diabetes among the population of patients presenting for care at primary health clinics, stratified by age, sex, and HIV status where possible?
- What proportion of diagnosed cases of these conditions are initiated on guideline-compliant treatment?
- What proportion of cases have satisfactory outcomes, based on current guidelines 12 months after diagnosis?
- For each condition, what proportion of patients are lost to care or discontinue treatment during the first 12 months after diagnosis?

Note that the impacts being assessed under Objectives 1-6 are the impacts of the interventions as implemented in the early phase of the national rollout of the guidelines. As is the case with program evaluations in general, results will reflect both intervention efficacy and implementation quality, which may in turn reflect the early learning stage of national policy implementation.

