# EVALUATION OF INTERVENTION EFFECTIVENESS (OBJECTIVES 1-5)

To achieve the first five objectives, we will test the effectiveness of five interventions included in the minimum package of adherence interventions using routinely collected data only. The interventions have been developed by the NDOH and will be implemented by the public sector clinics using their own staff and resources. Those interventions included in the evaluation were selected as having outcomes that could be assessed in a relatively short period of time, so that results can be used to refine the national guidelines and implementation. Below we detail each of the interventions and the populations we will use to evaluate the interventions.

We will use a matched cluster randomized design to evaluate the impact of each of the selected interventions. The National Department of Health, in consultation with the study team, will develop a short list of candidate primary health care clinics where early implementation of the package can occur. This short list will include proposed matched pairs of facilities which will be randomized to either implement the minimum package or not. Clinics will be matched on characteristics that are likely to affect study outcomes (patient volume, urban/rural location, current HIV viral suppression rate).

Because the interventions will be implemented clinic-wide and the evaluation will rely on routinely collected data only, we will include the entire patient population at each study site. All non-pregnant adult patients seeking HIV-related services at the study sites and eligible to receive one of the adherence interventions during the enrollment period will be included in the study through use of their clinic data. There will be no direct interaction with study subjects. Data will be collected from existing, routinely completed patient records, including clinic files, registers, cards, and databases. No additional data fields, beyond what are currently mandated under government guidelines, will be collected for the study. We assume that all study sites will follow the current guidelines for HIV care and treatment, dated December 2014[10] and the Primary Care 101 guide for TB, HIV, diabetes and hypertension care and treatment, dated 2013/14[15] as well as comply with the National Health Act of 2003.

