- *Setting*. Both sites in each pair should draw from the same type of community: urban; informal settlement; or rural.
- *Location*. Pairs should be located relatively nearby one another, to facilitate data collection and increase similarity of the catchment populations.

- *HIV viral suppression*. The clinics in the pair should have ART patient viral suppression rates within 10% percent of one another (if data available).

Letters indicating Provincial and District Department of Health authorization to work at each study site have been obtained and are attached. The final number of clinics selected remains at 24 clusters.

In each pair, one clinic will randomly be assigned to receive early implementation of the minimum package of interventions, while the other will continue to provide standard of care. Randomization will be done through a random number generator in Microsoft Excel with a 1:1 ratio of allocation to intervention and control clusters.

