| Overall impact (Objective 6) | Proportion of population in need at each clinic who achieve the short term primary outcomes defined above. | Proportion of population in need at each clinic who achieve the long term primary outcomes defined above. |
| Cost  (Objective 7) | Average cost per patient receiving an adherence intervention | Average cost per primary outcome achieved; average cost per 1000 patients receiving the observed mix of interventions |
| TB, hypertension, and diabetes (Objective 8) | For each condition, proportion of patients eligible for treatment who have 80% visit compliance in the first three months after diagnosis (S) and who achieve disease control at the six-month visit after diagnosis (L) as indicated in “Primary Care 101,” the NDOH’s guide for primary health clinic services[15]. The six-month visit will be represented by the visit closest to six months within the window of 5-8 months after diagnosis. The disease control indicators to be measured, with page references for Primary Care 101, are:  TB: cured or treatment completed indicated as the patient’s status at 6 months (page 57)  Hypertension: blood pressure controlled at 6-month visit, with control defined as < 140/90 (or 120/70–140/80 if diabetes, or <130/80 if CVD, heart failure or kidney disease) (page 74)  Diabetes: random glucose < 8 or HbA1c ≤ 7% at 6 month visit (page 71) | Among patients screened, prevalence of pre-diabetes elevated blood sugar (defined by Primary Care 101 as random glucose between 7.8 and 11) and pre-hypertension elevated blood pressure that require monitoring  Proportion of patients diagnosed with pre-diabetes or pre-hypertension who a) progress to diabetes and hypertension; or b) remain in care and receive appropriate monitoring for their condition over 12 months  Prevalence of diabetes, hypertension and TB among patients screened  Proportion of diagnosed patients initiated on appropriate treatment  Proportion of patients on treatment retained in care at 12 months. Loss to follow up will be defined as being 30 days late for a scheduled appointment.  Demographic and clinical characteristics of patients who do and do not achieve primary outcomes. |

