## **b. Sample Size**

Table 4 shows the sample size that is required to detect meaningful differences for Objectives 1-5 and for estimating precise rates for Objective 8. Each sample size is determined to measure our short term outcome for the objective. For Objectives 1-5, all calculations assume a site-clustered design with the clinic as the cluster; 24 clusters evenly split (randomized) between intervention and comparison groups; a coefficient of variation of 0.1, 80% power; and an alpha of 0.05.

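### The site-by-intervention interaction planned for Objective 6 cannot be estimated because each clinic is in one arm only, and the protocol names different outcomes for Objective 6 in different places

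*Protocol*

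**What the plan says.** **Allocation.** Protocol section 8.a: "In each pair, one clinic will randomly be assigned to receive early implementation of the minimum package of interventions". The other clinic of the pair continues standard of care. Section 10.b confirms "24 clusters evenly split (randomized) between intervention and comparison groups". Section 4 explains that whole clinic populations are included: "Because the interventions will be implemented clinic-wide and the evaluation will rely on routinely collected data only".

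**Analysis of Objective 6.** Section 10.d has three steps:

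1. An overall comparison: "we will analyze patient retention in care within intervention and comparison groups overall".
2. A comparison of packages: "We will include interaction terms between site and intervention to determine whether different packages of interventions produce different cumulative effects".
3. A weighting of the intervention effects by the eligible population at each site, to give the share of patients in need who can be expected to gain.

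Section 5 wants the result for each clinic and intends clinics in the intervention arm to be compared with one another.

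**Outcome of Objective 6.** The first research question in section 3.c is "What is the effect of the package of interventions on patient retention in care overall"; the second concerns the share of the population in need that benefits. Table 3 gives the primary outcome as "Proportion of population in need at each clinic who achieve the short term primary outcomes defined above" and the secondary outcome as "Proportion of population in need at each clinic who achieve the long term primary outcomes defined above". Neither cell lists retention.

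**The concern.** A site-by-intervention interaction asks whether the effect of the intervention differs from one clinic to another. That needs, in each clinic, patients under the intervention and patients under the comparison condition. A design with one arm per clinic never supplies both. The packages that actually differ between clinics would also arise from how each clinic implements the guidelines, which is not randomised.

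At stake is the second step of section 10.d. If it is carried out as written, ordinary differences between clinics could reach the Department of Health labelled as differences in package effect, and section 5 says these results are meant to refine expectations and models.

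The outcome question is separate. With retention in two places and other outcomes in Table 3, a reader cannot tell which result decides Objective 6, and the choice could be made after the data are seen.

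**Working it through.** The protocol states no sample size, power or alpha for Objective 6, so there is no figure to reproduce. The check is whether the model terms are estimable and whether the outcome statements agree.

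**Inputs from the protocol.** 24 clinics, 12 pairs, one arm per clinic (sections 8.a and 10.b); five cohorts per clinic with 30, 24, 24, 42 and 24 patients per cluster (section 4); coefficient of variation (CV) 0.1 (section 10.b).

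**Site by arm, read literally.**
- Cells needed: 24 × 2 = 48. Cells observed: 24.
- Intercept plus 23 site indicators: rank 24.
- The arm column is the sum of the indicators of the 12 intervention clinics, so adding it leaves rank 24.
- Each site-by-arm column equals that site's indicator (intervention clinic) or is all zeros (comparison clinic). With all of them there are 1 + 23 + 1 + 23 = 48 columns, and the rank is still 24.
- Degrees of freedom for the interaction: 24 − 24 = 0.

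Arm is lost as well, but only if site enters as fixed terms. With site treated as the cluster, as section 10.c does for Objectives 1-5, the overall arm effect remains estimable.

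**Other readings.**
- *Intervention means type of intervention.* Site by cohort has 24 × 5 = 120 cells and rank 120; adding cohort by arm leaves it at 120, so there are still no clinic-specific effects. With site and cohort as main effects only, the rank is 24 + 4 = 28, and cohort by arm raises it to 32. Those 4 contrasts say whether the five interventions differ in effect averaged over clinics, not whether clinics differ.
- *Each intervention clinic against the pooled comparison clinics.* One comparison mean plus 12 clinic means gives 13 parameters, 11 more than the two arm means. The 11 extra contrasts are differences among intervention clinics, with no clinic's own control level behind them.
- *Site means matched pair.* Pair plus arm has rank 13; pair by arm raises it to 24, giving 11 degrees of freedom. This can be fitted, but it is confounded with clinic-to-clinic variation.

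To gauge that confounding, an 11-df heterogeneity test with patient-level variance (nominal 5%) was simulated 5,000 times per setting with no true difference in effect. The outcome proportions 0.6 and 0.8 are assumptions. The 144 patients per clinic are 30 + 24 + 24 + 42 + 24. Clinics were drawn independently, so matching is assumed to explain none of the variation; the CV 0.05 column shows a smaller value.

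| Patients per clinic | Proportion | CV 0 | CV 0.05 | CV 0.1 |
|---|---|---|---|---|
| 30 | 0.6 | 7.8% | 13.0% | 33.9% |
| 30 | 0.8 | 7.2% | 23.3% | 70.8% |
| 144 | 0.6 | 5.2% | 32.4% | 86.7% |
| 144 | 0.8 | 5.5% | 72.7% | 99.2% |

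At the protocol's own CV, the test would report differing effects in 34% to 99% of trials in which there are none.

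**Outcomes side by side.**
- Section 3.c: retention first, then the share expected to benefit.
- Table 3: short-term outcomes primary, long-term outcomes secondary.
- Section 10.d: retention in step 1, unnamed outcome in step 3.

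The five short-term outcomes are ART start within 30 days, receipt of all medication (two cohorts), being alive, in care and re-suppressed, and return to care. Retention is one component of the fourth and is none of the five by itself.

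**The case against.** The strongest reply is that little of Objective 6 depends on the faulty sentence. This stands. The overall comparison of retention and the weighting step can both be done without the interaction, so a reader who infers that Objective 6 as a whole collapses goes further than section 10.d allows.

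A reader might also infer that every clinic-level impact reported under Objective 6 would be a clinic difference in disguise. The text does not support that. The clinic-level figure in section 10.d comes from weighting intervention effects by local eligible numbers. If pooled effects are used, those figures differ through population mix and not through any interaction coefficient.

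A third tempting inference is that the Table 3 primary outcome has no analysis, or that retention was slipped in. Neither holds. Retention is the first research question of Objective 6. The weighting step loosely addresses Table 3, since section 5 applies the effects from the Objective 1-5 data to the population in need, and section 10.c estimates effects for each primary outcome. What remains is narrower: Table 3 omits retention, step 3 does not name its outcome, and expecting to benefit is not the same as achieving an outcome.

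It could finally be said that Objective 6 is only indicative and enrols no patients of its own. That bears on how serious the point is. It does not make the interaction estimable.

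**Conclusion.** The point holds for one analysis step and for the outcome labels. The interaction has zero degrees of freedom for any 24 clinics with one arm each; this follows from the design and needs no assumption about effect sizes or variances. The nearest substitutes either average over clinics or mix effect differences with clinic differences. The 34% to 99% for the pair-by-arm test rests on the assumed proportions, a CV of 0.1, a patient-level error term and no gain from matching; at CV 0.05 the range is 13% to 73%.

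The conflict between sections 3.c and 10.d on one side and Table 3 on the other is one of wording, but it leaves the deciding outcome of Objective 6 open. This should be fixed. The randomised comparisons under Objectives 1-5 are not affected.

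**What to change.** In section 10.d:

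- Delete the site-by-intervention interaction.
- Estimate the overall package effect with cluster-level inference that respects the 12 matched pairs.
- Examine effect modification only through arm by pre-specified site or pair characteristics (province, size, setting), much as section 10.c already plans for Objectives 1-5. Label any comparison by components implemented as non-randomised.
- State that a single clinic's effect is not separately identifiable, and that the spread of the 12 within-pair differences includes ordinary clinic-to-clinic variation.
- State that the weighting step uses the pooled short-term effects from Objectives 1-5.

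Make section 3.c, Table 3 and section 10.d name the same primary outcome or outcomes. If retention is kept, list it in Table 3 with its rank stated; it should not be demoted without explanation, since it is the first research question.

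If population-weighted proportions are compared within pairs, use common weights for both clinics. For illustration, take about 80% for medication pickup and 30% for return to care (within the 20-35% in Table 4), with assumed mixes. A 70/30 clinic scores 0.7 × 80 + 0.3 × 30 = 65%, and a 50/50 clinic scores 0.5 × 80 + 0.5 × 30 = 55%. That is a 10-point gap with no intervention effect.

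The cost is one rewritten paragraph and aligned outcome entries, with no new data. The loss is any claim about an individual clinic's own impact, so the clinic-level aim in section 5 must be reworded to match.
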